### Recruitment 

AGYW who purchase a contraceptive method at a retail pharmacy study site will be recruited and enrolled. AGYW will be recruited into this trial following the purchase of contraception. Pharmacy staff will be aware of the study and asked to identify potentially eligible women at the point of contraceptive purchase. Pharmacy staff will explain the study to women who are potentially eligible and, if the woman expresses an interest in participating, will refer her to study staff. The study staff will then provide an in-depth explanation of the purpose and procedures of the study, in the language of the woman’s choosing, answer any questions the woman may have, and invite the woman to participate in the study. Participants will be informed that their participation is voluntary and that participation or nonparticipation in the study will in no way alter the nature of services that they receive at the pharmacy. If interested in participating, the study staff will screen the woman for eligibility, and, if eligible, the woman will provide written consent for their enrollment.

## Assignment of interventions: allocation

### Sequence generation 

Following pharmacy provider training, the study randomized 20 pharmacies 1:1 to either receive (*n* = 10) or not receive (*n* = 10) a nurse navigator arm to support PrEP delivery for AGYW. The pharmacy-level cluster randomization will be conducted using restricted randomization based on AGYW volume (i.e., monthly number of purchases made by AGYW clients) stratified by sub-county. Following study protocol training at an in-person event with staff from all 20 pharmacies, pharmacy staff were asked to select a ball with a random study arm assignment from a bag within each of the 10 groups to build camaraderie and demonstrate transparency of the randomization process.

### Concealment mechanism 

Since randomization occurred at the pharmacy level, it is impossible to blind study team members or participants to randomization assignments. However, procedures to minimize the influence of the unblinded nature of this study on outcomes are implemented. Randomization was only disclosed after all pharmacies were recruited and trained and signed agreements to participate in the study, following ethical approval. Ongoing data monitoring does not include information about study endpoints disaggregated by site or study arm. Only the study statistician will review data on study endpoints by study arm or facility.

### Implementation 

The randomization key of the data on study end points by study arm or pharmacy will be restricted to the data manager and statistician involved in the study.

## Assignment of interventions: blinding

### Who will be blinded 

N/A. The AGYW Pharmacy PrEP trial is an unblinded trial. Neither the participants nor the trial team will be blinded.

### Procedure for unblinding if needed 

N/A. The AGYW Pharmacy study is an open-label trial.

## Data collection and management

### Plans for assessment and collection of outcomes 

We will collect baseline data on demographic and behavioral characteristics, contraceptive history, education, marital status, income, relationship characteristics, HIV status and testing results, and clinical characteristics. At each visit, study staff will administer questionnaires to participants to assess sexual behavior, PrEP attitudes, use, and adherence. We will also measure IMB model-guided psychosocial moderating factors, including experience of IPV, symptoms of depression, socioeconomic status (SES), sexual and reproductive empowerment (SRE) and health, and PrEP use disclosure. We will assess SRE with the SRE-Kenya scale, which has been adapted and validated by our group for Kenyan AGYW. We will also capture PrEP-related side effects (e.g., nausea, headaches, dizziness) [27]. Fidelity will be monitored through QA/QC with direct observation of client-provider interactions using MEASURE Evaluation’s framework for monitoring quality of care in family planning services [28]. Hair samples (~ 50 strands) will be collected from all participants at every follow-up visit to objectively assess PrEP use and longitudinal analyses of PrEP use patterns.

HIV testing will be conducted at every visit per national guidelines. In a subset of four pharmacies, two from each study arm, we will conduct STI (for gonorrhea and chlamydia). The study utilizes the Cepheid Gene X-pert machine, a 4-module NAAT analyzer for real-time PCR testing of CT/NG and TV assays with expedited partner treatment for those with STI diagnoses to allow for analyses of STI incidence by arm.

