### Intervention description 

In both arms, AGYW receive standard PrEP services at the pharmacy, which entail a pharmacy provider using a prescribing checklist to identify individuals with risk for HIV acquisition and at low risk of any drug contraindications, counsel them on PrEP adherence (per national guidelines), test for HIV, and prescribe/dispense PrEP with remote clinician oversight. All participants offered PrEP self-select either daily oral PrEP pills or the DPV-VR. All participants are provided with a study phone number to call free of charge for clarifying questions or concerns with PrEP use (Fig. 3).

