### Sample size 

To account for between-cluster variability, sample size calculations incorporated the coefficient of variation between pharmacies (*k*) [25, 26]. Assuming each cluster enrolls 95 (accounting for 15% attrition) AGYW and that 30% of participants achieve the primary outcome of PrEP persistence at 10 months (31) in the standard pharmacy PrEP model arm (control arm) arm with a coefficient of variation between clinics (*k*) of 0.05, 10 clusters per arm will give 90% power to detect a 15% absolute difference in proportions and a two-sided test with *α* = 0.05. Typical (*k*) values are 0.15 to 0.5 for rare binary outcomes and 0 to 0.05 for non-rare outcomes [25, 26]. Assuming 15% attrition, will enroll a final sample of 1900 ANC attendees at 20 sites (95 women per site; 950 women per arm).

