## Statistical methods

### Statistical methods for primary and secondary outcomes 

We will conduct an intention-to-treat analysis with the primary exposure of randomization arm (pharmacy-based PrEP delivery with nurse navigators vs. standard pharmacy-based PrEP delivery without nurse navigators) to test the hypotheses that incorporating nurse navigators within a pharmacy-based PrEP delivery model will improve PrEP initiation, persistence, and adherence among AGYW seeking contraception at retail pharmacies.

For analyses of our primary outcomes, we will use a log-binomial regression model to estimate relative risks and 95% CI. We will include any imbalanced baseline demographic, clinical, or behavioral characteristics between arms as independent variables in an adjusted model. If primary outcome data are missing or in cases of loss to follow-up, we will assume PrEP discontinuation/nonadherence to fit the most conservative models.

Secondary outcome analyses will include PrEP method selection, predictors of non-adherence, and STI incidence and cofactors. For data analysis approaches, we will use log-binomial regression with robust standard errors for the former two and Anderson-Gill survival analysis for the later. Exploratory analyses will include HIV incidence, quality of care, and contraceptive method mixed by randomization arms (Table 1). We will use survival analysis, generalized estimating equation models with logistic link, and robust standard errors and log binomial regression respectively.

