### Methods for additional analyses (e.g., subgroup analyses) 

Subgroup analyses will involve data from all AGYW at the enrollment visit to evaluate the effect of STI testing on PrEP initiation. We will also evaluate the association between offering STI testing at PrEP initiation and time-to-discontinuation using Cox proportional hazards models. We will have sufficient power to detect differences in the frequency of PrEP persistence of 14% or 60% between AGYW offered and not offered STI testing, assuming a 2-sided test with alpha = 0.05 and 80% power (*β* = 0.20). All models will use robust standard errors.

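### The covariate rule for the primary models would leave out pharmacy STI-testing status, a known design factor, at an avoidable cost in precision if STI testing affects PrEP use (minor)

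*Protocol article*

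**What the plan says.** **Where STI testing happens.** Under Plans for assessment and collection of outcomes, the protocol states: "In a subset of four pharmacies, two from each study arm, we will conduct STI (for gonorrhea and chlamydia". The same paragraph adds "expedited partner treatment for those with STI diagnoses to allow for analyses of STI incidence by arm". So 2 of 10 pharmacies in each arm provide this service.

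**What standard care is.** Intervention description states: "In both arms, AGYW receive standard PrEP services at the pharmacy". It then lists a prescribing checklist, counselling, HIV testing and dispensing under remote oversight. STI testing is not on that list.

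**What the plan does with the factor.** Methods for additional analyses sets out "to evaluate the effect of STI testing on PrEP initiation", and also the "association between offering STI testing at PrEP initiation and time-to-discontinuation using Cox proportional hazards models". It mentions 14% as a detectable difference in persistence between women offered and not offered testing.

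**The primary analysis.** Statistical methods for primary and secondary outcomes states: "For analyses of our primary outcomes, we will use a log-binomial regression model to estimate relative risks and 95% CI". The only covariates named are participant features at baseline that prove unevenly distributed between the arms. Women lost to follow-up count as having stopped PrEP.

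**The sizing.** Sample size assumes 30% persistence "in the standard pharmacy PrEP model arm (control arm) arm with a coefficient of variation between clinics" of 0.05, ten clusters per arm, 95 women each and a 15-point difference. It makes no separate allowance for the STI subset.

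**The concern.** The protocol identifies a pharmacy-level service, sets out to study it as a possible influence on initiation and discontinuation, and then states a covariate rule for the primary models that cannot select it. STI-testing status is not a participant characteristic at baseline, and at 2 v 2 it is never imbalanced.

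If STI testing does shift persistence, the four pharmacies sit apart from the other sixteen. An unadjusted model counts that spread as unexplained between-pharmacy variation. With 20 clusters, such variation can dominate the standard error. The estimate itself is not made less stable, because the split is fixed and even; the standard error attached to it is too large. Intervals are then wider than they need be, and power is given away.

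**Working it through.** **1. Inputs.** From Sample size: p0 = 0.30, p1 = 0.45, c = 10 pharmacies per arm, k = 0.05, m = 95 women. A 15% loss would leave 95 × 0.85 ≈ 81, so both are shown. From Plans for assessment: a fraction 2/10 = 0.2 of pharmacies per arm offer STI testing. *Assumed, not given:* an additive shift d in those pharmacies, equal in both arms. The value d = 0.14 is borrowed from the detectable difference in Methods for additional analyses. It is not a predicted effect, and the sentence it comes from, which pairs 14% with 60%, is unclear.

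**2. The plan's own power figure.** The Hayes–Bennett formula is c = 1 + (1.96 + 1.2816)² × {[p0(1−p0) + p1(1−p1)]/m + k²(p0² + p1²)}/(p1 − p0)². At k = 0.05 it needs c = 3.59 (m = 95) or 3.98 (m = 81) for 90% power. Ten clusters therefore give more than 99.9%, not the stated 90%. About 90% at ten clusters corresponds to k ≈ 0.22 (c = 9.86 at m = 95). That mismatch is a separate matter. It is used here only to show a second value of k.

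**3. Adding the STI subset.** A shift d in one fifth of the pharmacies moves each arm's mean by 0.2d and adds variance 0.2 × 0.8 × d² per arm:

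V = [p0(1−p0) + p1(1−p1)]/m + k²(p0² + p1²) + 2 × 0.16 × d², with p0 = 0.30 + 0.2d and p1 = 0.45 + 0.2d; SE = √(V/10).

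At d = 0.14 the arm means become 32.8% and 47.8%, and the difference stays at 15 points. The added between-pharmacy SD is √0.16 × 0.14 = 5.6 points, against 0.05 × 0.30 = 1.5 points in the sizing.

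**4. Standard error at k = 0.05.**
- m = 95, no shift: V = 0.00482 + 0.00073 = 0.00555, SE = 0.0236. With the shift: V = 0.00495 + 0.00084 + 0.00627 = 0.01206, SE = 0.0347, which is 47% larger.
- m = 81: SE goes from 0.0253 to 0.0359, which is 42% larger.

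**5. Power** (cluster-level t test, noncentral t; 18 df unadjusted, 17 df with the STI term, which removes the last part of V):

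| k | m | d | unadjusted | adjusted |
|---|---|---|---|---|
| 0.05 | 95 | 0.14 | 98.3% | >99.9% |
| 0.05 | 81 | 0.14 | 97.6% | >99.9% |
| 0.22 | 95 | 0 | 90.2% | 90.0% |
| 0.22 | 95 | 0.05 | 87.9% | 88.9% |
| 0.22 | 95 | 0.10 | 82.9% | 87.6% |
| 0.22 | 95 | 0.14 | 77.2% | 86.6% |

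At k = 0.05, unadjusted power does not come down to about 90% until d is about 20 points.

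**6. Simulation check.** With the 2 v 2 split held fixed (m = 81, d = 0.14), the mean estimate is 15.0 points with or without the STI term. Power is 99.7% unadjusted and 100% adjusted at k = 0.05; at k = 0.25 it is 74.7% and 83.6%. The unadjusted type I error is about 0.4% at k = 0.05 and 2% at k = 0.25, against a nominal 5%. This confirms that the reported standard error is too large and the error is on the conservative side.

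**The case against.** The case against is substantial.

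- **It may belong to the analysis plan.** Interim analyses refers to a statistical analysis plan, which is not shown and could name STI-testing status as a covariate. That stands as a reason for low severity. It does not dispose of the point, because the article does state a covariate rule, and that rule as written does not reach this factor.
- **No harm on the plan's own inputs.** At k = 0.05 and a 14-point shift, power stays about 98%, well above the 90% sought. This stands. The drop to 77% needs both a large shift and k = 0.22, which is back-solved and lies above the 0 to 0.05 that the protocol cites for non-rare outcomes.
- **No bias.** With a common additive effect this stands in full for the absolute difference.
- **Limits of the calculation.** It covers persistence only and uses a cluster-level t test in place of the log-binomial model. Both limits stand.

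Three stronger readings are tempting. A reader might infer that the investigators expect STI testing to change PrEP use; the text only plans to evaluate an effect and an association. A reader might infer that the comparator is no longer standard pharmacy PrEP; STI testing is present equally in both arms, its purpose is stated, and even a 14-point shift moves the control rate only from 30% to 32.8%. A reader might infer that the arm comparison is confounded; a 2 v 2 split does not produce that under a common effect.

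**Conclusion.** The point holds as a minor one. A known, balanced design factor falls outside the stated covariate rule. If STI testing affects the primary outcomes, the reported precision will be worse than it need be.

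The size depends on two quantities that the documents do not settle: the STI-testing effect and the true between-pharmacy variation. For persistence, the loss runs from about 1 point of power (5-point shift, k = 0.22) to about 9 points (14-point shift, k = 0.22). At the planned k = 0.05 the cost of a 14-point shift is wider intervals, with little loss of power. If STI testing has no effect, nothing is lost.

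Two qualifications apply. The protocol reports relative risks: a common additive shift of 14 points would move the ratio from 45/30 = 1.50 to 47.8/32.8 = 1.46, whereas a purely multiplicative effect would leave it unchanged. If the shift arose in the control arm alone, the 15-point difference would shrink to 15 − 0.2 × 14 = 12.2 points, and a simple covariate would not restore it. Nothing in the documents points to such a difference between arms.

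**What to change.** In Statistical methods for primary and secondary outcomes, name pharmacy STI-testing status (offered / not offered) as a prespecified fixed covariate in the models for initiation, persistence and adherence, whatever baseline imbalance is seen. If the analysis plan already does this, the article's description of the adjusted model should say so.

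The change is one of wording, and the variable is known for every pharmacy. It uses one cluster-level degree of freedom (18 to 17). With no STI effect, that takes power from 90.2% to 90.0% at k = 0.22 and 95 women per pharmacy. Fixing it in advance also avoids a data-driven choice in an unblinded trial.

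Two additions are optional: a sentence in Intervention description noting the STI subset in both arms, and a repeat of the arm comparison in the 16 pharmacies without STI testing. The latter drops a fifth of the clusters and adds little, since the mix is the same in both arms.

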### Outcomes 

Our primary outcome is PrEP initiation among AGYW seeking contraception at retail pharmacies at enrollment and evidence of self-reported use at 1-month post-use (Table 1). Our second primary outcome is PrEP persistence at 10 months among AGYW who initiated PrEP. Our third primary outcome will be PrEP adherence defined as either TFV or DPV hair levels (depending on PrEP method) at 10 months.

**Table 1 Tab1:** Primary, secondary, and exploratory outcomes of the trial

Outcome		Definition
Primary	PrEP initiation	Binary endpoints (yes, no) of self-reported use of oral PrEP or DPV-VR at 1 month after acceptance at enrollment. Self-reported PrEP use will be considered initiation. If a participant declined or reported not using PrEP after acceptance, the participant will be considered non-initiated
	PrEP persistence	Binary endpoints (yes, no) of self-reported use of oral PrEP or DPV-VR at 10-month after acceptance at enrollment. Self-reported PrEP use will be considered persistence. If a participant declined PrEP or reported not using PrEP after acceptance or discontinued PrEP before 10 months will be considered non-persistent [24]
	PrEP adherence	Binary endpoints (yes, no) of detectable TDF levels in hair > 0.038 ng/mg or DPV levels > 0.0248 n/mg at 10-month visit will be considered adherent. If a participant stopped PrEP use or exited study before 10 months (i.e., no hair sample collected), the participant will be considered non-adherent
Secondary	PrEP method selection	Binary endpoints (yes, no) of self-reported DPV-VR compared to daily PrEP when offered at enrollment
	Predictors of non-adherence	Factors associated with poor adherence (< 90% adherent on PrEP or discontinuation) will include demographics, relationship/partner characteristics, psychosocial factors, socio-economic status, low health/HIV literacy, fear of disclosure
	STI incidence and cofactors	Frequency of STI (syphilis, gonorrhea, and chlamydia) detection at follow-up will be compared between randomization arms
Exploratory	HIV incidence	Frequency of HIV diagnosis at follow-up visits will be compared between randomization arms
	Quality of care	Binary endpoints (yes, no) based on MEASURE Evaluations indicators for quality of care in family planning (e.g., Did the provider ask if you were having a problem with your FP method?)
	Contraceptive method mix	Binary endpoints (yes, no) or LARC use will be compared between randomization arms and distribution of contraceptive method types

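### Two STI-testing pharmacies per arm are too few for the planned between-arm STI comparison, and the power figure for STI testing does not state the inputs it rests on

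*Protocol article*

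**What the plan says.** Outcomes, Table 1, gives the secondary outcome: "Frequency of STI (syphilis, gonorrhea, and chlamydia) detection at follow-up will be compared between randomization arms". Plans for assessment and collection of outcomes confines testing to a subset: "In a subset of four pharmacies, two from each study arm, we will conduct STI (for gonorrhea and chlamydia". The same section gives the purpose of the assays: "to allow for analyses of STI incidence by arm". Statistical methods for primary and secondary outcomes sets the model: "we will use log-binomial regression with robust standard errors for the former two and Anderson-Gill survival analysis for the later". Nothing marks the arm comparison as descriptive, and no event rate, precision or power is given for it.

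The pathogens differ by section. Table 1 has syphilis, gonorrhea and chlamydia. The data collection section names gonorrhea and chlamydia, then describes CT/NG and TV assays. The Discussion names gonorrhea and chlamydia.

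Methods for additional analyses plans a second contrast: the effect of STI testing on PrEP initiation, and the association of offering it with time to discontinuation. It claims "sufficient power to detect differences in the frequency of PrEP persistence of 14% or 60% between AGYW offered and not offered STI testing", two-sided at 5% with 80% power, and says that all models use robust standard errors.

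**The concern.** The pharmacy is the randomized unit. With two tested pharmacies per arm, a difference in STI rates between arms cannot be told apart from ordinary differences between a few sites. An analysis of individual women, or a robust variance that needs many clusters, can make such a difference look precise. A statistical analysis plan can choose the variance estimator but cannot add clusters.

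The second contrast has a related weakness. As the data collection section implies, it sets four pharmacies that offer STI testing against sixteen that do not. The article does not say that the four were chosen at random, and the power sentence cannot be matched to this contrast without guessing its inputs.

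**Working it through.** **Inputs from the article.** Two tested pharmacies per arm; "95 women per site; 950 women per arm"; 15% attrition ("Assuming 15% attrition, will enroll a final sample of 1900 ANC attendees at 20 sites"), so 95 × 0.85 = 80.75 women per pharmacy. From Sample size: 30% control-arm persistence, k = 0.05, and typical k of 0.15–0.5 for rare and 0–0.05 for non-rare binary outcomes.

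**Assumed, because not stated.** STI incidence over 10 months of 5–30% (for the simulation, 30 per 100 person-years, with 80.75 × 10/12 ≈ 67 person-years per pharmacy), and k for STIs.

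**1. STI incidence by arm, 2 v 2 pharmacies.**

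*Permutation test.* There are C(4,2) = 6 allocations, so the smallest two-sided p is 2/6 = 0.33.

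*Cluster-level t test.* There are 2 degrees of freedom and the critical value is 4.30. The variance of the difference is the sum over arms of [p(1−p)/m + k²p²]/2, with m = 80.75. For 20% v 10% at k = 0.15:

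- control: 0.16/80.75 + 0.0225 × 0.04 = 0.00288
- intervention: 0.09/80.75 + 0.0225 × 0.01 = 0.00134
- standard error: √[(0.00288 + 0.00134)/2] = 0.046
- ratio: 0.10/0.046 = 2.18, against 4.30; power 25%

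Power to detect a halving:

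| Incidence | k = 0.05 | k = 0.15 | k = 0.25 |
|---|---|---|---|
| 5% | 11% | 11% | 10% |
| 10% | 18% | 16% | 14% |
| 20% | 30% | 25% | 19% |
| 30% | 42% | 32% | 22% |

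At 5% or 10% incidence no reduction, however large, reaches 80% power.

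*Simulated type I error* (gamma-Poisson counts, no true arm difference):

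- A robust variance on four clusters with a normal critical value has about 30% at every k examined.
- A model ignoring pharmacy has about 5% at k = 0.05, 10% at k = 0.15 and 42% at k = 0.5.
- The 2-df t test holds about 5%.

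**2. The 14% or 60% figure.**

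*Reproducing it.* With 190 per group (two pharmacies of 95), 30% v 44%, no clustering and no attrition, the standard error is √[(0.21 + 0.2464)/190] = 0.049. The ratio is 0.14/0.049 = 2.86 and power is about 81%. So 14 points can be reproduced, but for a 190 v 190 comparison, not for offered v not offered.

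*The contrast implied.* Four pharmacies (380 women) against sixteen (1,520). With 30% v 44%, k = 0.05 and 95 per pharmacy, the variance is (0.21/95 + 0.0025 × 0.09)/16 + (0.2464/95 + 0.0025 × 0.1936)/4 = 0.00092. The standard error is 0.030, the ratio 4.61, and power on 18 df is 99%. Over k, without and then with attrition:

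| k | Difference with 80% power (points) | Power for 14 points |
|---|---|---|
| 0.05 | 8.7 / 9.4 | 99% / 98% |
| 0.15 | 13.1 / 13.7 | 84% / 82% |
| 0.20 | 16.8 / 17.3 | 68% / 66% |

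*The 60%.* On 30%, 14 points is 0.14/0.30 = 47% relative, and 60% relative is 18 points. The two agree only at a reference of 0.14/0.60 = 23%, which the article does not state.

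**The case against.** Four points deserve weight.

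- A reader might infer that no valid test on 2 v 2 pharmacies can reach 5%. That is true of the permutation test only. A 2-df cluster-level t test holds its level and can reject; its fault is very low power. The 0.33 floor also assumes unrestricted allocation, whereas Sequence generation describes restricted randomization drawn within 10 groups. Restriction can only reduce the six allocations, so it cannot lower the floor.
- Ignoring pharmacy does little harm if k is as low as 0.05. This stands. The damage depends on k, which the article does not give for STIs; at the 0.15–0.5 it quotes for rare outcomes the inflation is material.
- A reader might infer that the 14-point figure is irreproducible or an overclaim. Neither is supported. It reproduces at 190 v 190, is close to the 80%-power difference for 4 v 16 at k near 0.15, and is conservative at k = 0.05. Moreover, 30% is the control-arm rate of the primary comparison, while this analysis pools both arms: under the plan's 30% and 45% the midpoint is 37.5%. The 30% reference and the 4 v 16 split are therefore inferences.
- The article already calls the time-to-discontinuation analysis an association. Powering it on persistence is only a small mismatch, because Table 1 counts stopping before 10 months as non-persistence. How clustering enters a secondary model may be left to the analysis plan. This removes some of the criticism, but does not supply the missing scale and reference or change the number of tested pharmacies.

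**Conclusion.** The point holds in this limited form. Two pharmacies per arm cannot support an inferential between-arm STI comparison: the valid cluster-level test has about 10–42% power for a halving, a four-cluster robust variance has about 30% type I error, and a model ignoring pharmacy is acceptable only if k is near 0.05. The permutation floor needs no assumption about STI rates. The power and error figures rest on assumed incidence and k, shown as ranges.

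The pathogen lists disagree, so the secondary endpoint is not fixed: no syphilis assay is described, and TV is assayed but is in no outcome definition.

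The 14% or 60% sentence is not shown to be wrong. It lacks the inputs needed to read it and does not match the contrast implied by four testing pharmacies out of twenty. Since the outcome is secondary, the primary analyses are unaffected.

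**What to change.** - Report STI rates by pharmacy and by arm descriptively, with no between-arm p-value. Keep pooled STI incidence and its cofactors in the four pharmacies as the objective.
- Reconcile the pathogens in Table 1 with the assays actually run.
- Restate the power sentence for the actual contrast: number of pharmacies and women on each side, reference persistence, absolute or relative scale, k, and cluster-level degrees of freedom. Show a range of k; the values above illustrate the calculation and are not figures to adopt.
- Describe the STI-testing analysis as a non-randomized association, adjusted for arm and clustered on pharmacy. If the four pharmacies were chosen at random, say so and say how.

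The cost is wording and one downgraded claim. No further testing is needed.
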